### Setting

For those who are interested in participating in the trial, cardiologist and study staff will confirm if they have eligibility criteria, and the appointment will be set for their first visit. In the first visit, the potential participants will have the proposals of the research project fully explained to them, and all participants will be asked to fill in the consent form. A general information questionnaire, including demographic information, disease history, the type and dosage of their medications, occupation, education and the smoking status, physical activity questionnaire, and three food recall questionnaire will be completed from each participant. The next visit will be after 2 weeks run-in period of weight maintenance, when baseline data including body weight and fasting blood sample will be obtained and the patient will be instructed to collect urine within the next 24 h and an ABPM device will be installed. After 24 h, the collected urine sample will be delivered and the results of the ABPM device will be stored. The patient will be given barberry or placebo packages and instruction on how to record their consumption. The next meeting will be at the end of the study to collect end-of-study data.

### Sample size

Sample size calculations were carried out using G*Power V.3.1.9.2 software [25]. The sample size was calculated based on data from Tjelle et al. [15], a relatively similar polyphenol-rich berry juice intervention study that observed a reduction in SBP of 6.2 mmHg compared to placebo. Assuming equal standard deviation in both group and by considering pooled value of the standard deviation = 8.8, a significance level of *α* ≤ 0.05 and statistical power of 80%, the minimum sample size will be 66 patients will be required to detect a change of this size in the SBP level. To account for a drop-out rate of approximately 20%, we plan to recruit 80 participants (40 randomized to each group).

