**Methods/design:**

This is an 8-week, prospective, single-blinded, parallel assigned, randomized controlled clinical trial (RCT) in which eligible men and women with hypertension and other cardiovascular risk factors will be randomized to either placebo powder (PP; containing 9 g maltodextrin, 1 g citric acid, 1 g milled sucrose and edible red color (*n* = 37)) or barberry powder (BP; containing 10 g milled dried barberry and 1 g of milled sucrose (*n* = 37)) groups. At baseline and after 8 weeks of intervention, plasma lipids and inflammatory markers, 24-h urinary nitrite/nitrate and sodium excretion, and 24-h ambulatory blood pressure monitoring (ABPM) will be measured. Anthropometric measures and dietary assessment will be performed as well. Data analysis will be done using SPSS version-21 software.

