### Participant recruitment

In this clinical trial, we will recruit a total of 80 participants both men and women (each group 40) with hypertension and other cardiovascular risk factors (diabetes and/or hyperlipidemia and/or smoking) in Tehran, the capital of Iran. Volunteers among patients with a previous history of hypertension who have a medical record in the academic hospital (Rajaei Cardiovascular, Medical & Research Center, Tehran, Iran) and are regularly visited in the hospital clinics every 4–6 months if they meet the eligibility criteria will be recruited. Besides, by placing an advertisement in the hospital, other volunteer people who are referred to the hospital if they meet the eligibility criteria are also included in the study. To guarantee achieving adequate participant enrolment, the clinic staff at the hospital will be informed about the study, and informational conversation with patients will be held.

The trial is due to last 9 months. This assumes 5 months for participant recruitment and intervention, 2 months for laboratory testing, 1 month for data preparation and analysis by SPSS software, and 1 month to write the study report. The study protocol has been reported in accordance with the Standard Protocol Items: Recommendations for Clinical Interventional Trials (SPIRIT) guidelines [24] (Additional file 1, SPIRIT Checklist). The trial schedule is shown in Table 1. Informed consent will be obtained from all subjects before collecting any information. After reviewing the consent forms and answering any probable questions by study staff, those who are interested will be asked to sign the forms. A copy of the consent form will be given to participants and all original signed consent forms will be kept by the study staff (Additional file 2, consent form).

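### The planned number to randomise is 37 per group in the abstract but 40 per group in the body; as a minor further slip, 80 recruits do not quite cover a 20% drop-out

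*Protocol article*

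**What the plan says.** **Abstract, Methods/design.** Eligible participants will be randomised to placebo or barberry, and each arm carries the figure 37. The barberry arm reads "10 g milled dried barberry and 1 g of milled sucrose (*n* = 37", and the placebo arm has the same number. The total is 74.

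**Participant recruitment.** The text says "we will recruit a total of 80 participants both men and women (each group 40".

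**Sample size.** The reference study "observed a reduction in SBP of 6.2 mmHg compared to placebo". The calculation was done "by considering pooled value of the standard deviation = 8.8", with "a significance level of *α* ≤ 0.05" and 80% power, and concludes that "the minimum sample size will be 66 patients". It then says "To account for a drop-out rate of approximately 20%, we plan to recruit 80 participants (40 randomized to each group".

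**Data management and monitoring.** Participant codes run from 1 to 80.

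**Statistical analyses.** The analysis is per protocol and restricted to participants who complete the study.

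**The concern.** The number to be randomised is one of the few figures against which a finished trial is later checked. Here the abstract and the body disagree by 6 participants. Both describe the plan in the future tense, and neither is superseded text. A reader of the abstract alone would take 74 as full enrolment, while a reader of the body would see 74 as 6 short. The text does not say which figure is the target.

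The second issue is smaller. The Sample size section presents 80 as the number that protects a minimum of 66 against roughly 20% loss. Because the analysis includes completers only, each drop-out comes straight off the analysed number, so this allowance is what preserves the stated power.

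**Working it through.** **Inputs, all from the Sample size section unless noted**
- Difference in systolic pressure: 6.2 mmHg
- Standard deviation, equal in both groups: 8.8
- Significance level 0.05. Sidedness is not stated; two-sided is assumed.
- Power: 80%
- Required number: 66; drop-out: approximately 20%; planned recruitment: 80
- Abstract: 37 per group

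**Step 1: reproduce the 66.** The standardised difference is 6.2/8.8 = 0.7045. A two-sample t test with the non-central t distribution, two-sided 5% and 80% power, needs 32.6 per group. This rounds up to 33, or 66 in total, with power 80.5%. The plan's figure is reproduced exactly. A one-sided test would need 25.6, so 26 per group or 52 in total, which supports the two-sided reading.

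**Step 2: can 37 per group be derived from the plan's figures?**

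| Possible meaning | Value | Equal to 37 per group (74)? |
|---|---|---|
| Completers required per group | 33 | No |
| 40 per group less 20% | 40 x 0.80 = 32 | No |
| 66 inflated by division | 66/0.80 = 82.5 | No |
| 66 inflated by multiplication | 66 x 1.20 = 79.2 | No |

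Read backwards, 74 recruits leave 66 only if loss is at most 1 - 66/74 = 10.8%. No drop-out rate near that appears in the text.

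**Step 3: does 80 cover 20% loss?**
- Needed: 66/(1 - 0.20) = 82.5, so 83, or 84 (42 per group) with equal arms.
- Left from 80 at 20% loss: 80 x 0.80 = 64, or 32 per group, which is 2 below 66.
- Largest loss that still leaves 66 from 80: 1 - 66/80 = 17.5%.
- 66 x 1.20 = 79.2, which rounds up to 80. The stated figure is therefore consistent with multiplying by 1.2 instead of dividing by 0.8.

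**Step 4: the effect on power (same t test, difference and standard deviation)**

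| Completers | Per group | Power |
|---|---|---|
| 66 | 33 | 80.5% |
| 64 (80 less 20%) | 32 | 79.2% |

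The cost of the slip is 80.5 - 79.2 = 1.3 percentage points.

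**The case against.** On the drop-out allowance, the case for leaving the text alone is fairly strong.

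- The text says approximately 20%, and 17.5%, at which 80 leaves exactly 66, is arguably within that phrase. Even at exactly 20% the gap is 2 patients.
- The normal approximation needs only 32 per group, so the gap is no larger than the difference between two standard formulas. The plan's own figure is 66, however, so the slip against its own minimum remains.
- The power figures are for an unadjusted t test, and the Statistical analyses section also provides for analysis of covariance on baseline. Suppose 8.8 is an unadjusted standard deviation, which the article does not say. Dividing 0.7045 by the square root of (1 - r²), a baseline correlation of r = 0.15 brings power at 32 per group to 80.1%, and r = 0.3 to 82.8%.
- The section shows no inflation formula, so multiplication by 1.2 is an inference, not something the document states.

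All of this stands, and it makes this part minor.

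A reader might infer that the trial is materially underpowered, for example by taking 20% off 74 to reach about 59 completers. The documents do not support that. The drop-out allowance is attached to 80, not to 74, and three sections of the body agree on 80. The 59-completer scenario combines two incompatible plans. Nor can one say flatly that the trial lacks 80% power, because the shortfall depends on exactly 20% loss and an unadjusted analysis.

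None of this answers the 37 against 40 contradiction. Agreement among three body sections suggests that the abstract is the outlier, but the article nowhere says so.

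**Conclusion.** The article is wrong as written and should be corrected.

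- **Main point.** Two planned randomised totals, 74 and 80, stand side by side unexplained, and 74 cannot be obtained from 66 completers with about 20% drop-out. This rests only on comparing the sections and needs no modelling assumption.
- **Minor point.** Recruiting 80 falls short of its stated purpose by 2 completers at exactly 20% loss, with power of 79.2% instead of 80.5%. This assumes a two-sided 5% unadjusted t test, a difference of 6.2 mmHg, a standard deviation of 8.8 and analysis of completers only.

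The base requirement of 66 is correct. Neither point calls the design into question.

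**What to change.** 1. Use one randomised number throughout. The body supports 40 per group, so correct the abstract from 37 to 40 in both arms, subject to the sponsor confirming that 80 is the target.
2. In the Sample size section, replace the sentence on drop-out with wording such as: 80 participants yield at least 66 completers if drop-out is at most 17.5%; at 20% drop-out, 64 completers give about 79% power.

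The cost is wording only, with no change to enrolment or analysis. The stated drop-out allowance, or the power at 20% loss, becomes slightly less favourable. If the sponsor prefers to keep a full 20% allowance, the matching number is 84 (42 per group), which is 4 more participants; the size of the slip does not require this.

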### Run-in

Hypertensive patients who have other cardiovascular risk factors will be entered into the 2-week maintenance weight program after the above steps have been taken. Participants will be asked not to change their lifestyle and keep researchers informed of any changes including diet, physical activity, and medication use. At the end of the first visit, a paper sheet will be given to the individuals, containing the description of the study, a date for the next visit, and the contact number. The presence of this run-in period is essential for maintaining their weight, as well as to test the participants’ motivation to continue the intervention.

### Randomization/blinding

Participants will be randomized to receive either the barberry or the placebo product. The randomization will be performed with the aid of a sequence generated by using a random number table. For this purpose, each row of the table was considered as a block, and from the left, in the order in the table, odd numbers were considered as group A and even numbers were considered as group B. If the first two allocations were for one of the A or B, the next two allocations were considered for the second group. The sequence of each block was placed in a sealed opaque envelope. Diabetes and hyperlipidemia are two other major CVD risk factors that may coexist with hypertension. To achieve a balanced distribution of these risk factors in each of the study groups, stratified block randomization will be performed, with four strata: with a history of diabetes, without a history of diabetes, receiving statins, and not receiving statins. A block size of 4 within each stratum will be used, with a 1:1 randomization between the two groups.

This trial has a single-blinded manner. Patients are blinded to the type of product they are consuming, but the main investigator who assigns patients to intervention or placebo groups is not blinded. Placebo and barberry powdered products are given to patients in undetectable non-transparent packaging.

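### One envelope holds a whole block of four and the assigning investigator is unblinded, so opening it for a block's first patient reveals that block's other three allocations

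*Protocol article*

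**What the plan says.** All the key statements are in the protocol article, Randomization/blinding.

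- Unit of concealment: "The sequence of each block was placed in a sealed opaque envelope".
- Block size and ratio: "A block size of 4 within each stratum will be used, with a 1:1 randomization between the two groups".
- How a block is filled: odd numbers give A and even numbers give B, with the rule "If the first two allocations were for one of the A or B, the next two allocations were considered for the second group".
- Strata: "with four strata: with a history of diabetes, without a history of diabetes, receiving statins, and not receiving statins".
- Who assigns: "the main investigator who assigns patients to intervention or placebo groups is not blinded".

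The section on Setting adds that "cardiologist and study staff will confirm if they have eligibility criteria". It does not say that these people are separate from the person who assigns. Setting and Run-in put consent, a two-week run-in and the baseline measurements before the packages are handed over. The opaque wrappers described under Randomization/blinding and under Study intervention and implementation keep the product hidden from patients. They do nothing to hide upcoming allocations from the assigner.

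**The concern.** Concealment requires that whoever enters or schedules a patient cannot know which arm that patient will get. Here the sealed unit is the block. An envelope protects the first allocation in it, but once opened it shows the next three. The article describes no separate covers inside the envelope, no third-party allocation and no varied block size.

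At stake is selection bias in the primary comparison of systolic blood pressure. Someone who knows the next allocation in a stratum can, without intending to, influence who stays through run-in or who is booked into which slot. Automatic 24-hour monitoring limits measurement bias, but selection acts before measurement. The covariance analysis under Statistical analyses adjusts for baseline levels. It would not correct an imbalance in unmeasured traits such as motivation or adherence.

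**Working it through.** The plan states no figure for predictability, so there is none to reproduce. The check counts how many allocations are known with certainty before they are made.

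**Inputs.** Block of 4, two A and two B, one block per envelope, the odd/even filling rule and an unblinded assigner (all Randomization/blinding). 80 patients (Sample size; the Abstract gives 37 per group, which does not change the proportions for filled blocks). Assumptions:

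- The assigner sees the opened envelope.
- Odd and even are equally likely.
- When the first two allocations differ, the third is random and the fourth is forced, as 2:2 requires.

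**1. As written, one envelope per block.** Position 1 is unknown; positions 2, 3 and 4 are known.

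- Known share = 3/4 = 75%.
- If all blocks fill: 0.75 × 80 = 60 patients.

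**2. Part-filled blocks.** Each opened envelope yields one unknown allocation, so known = 80 − envelopes opened. Take four non-overlapping strata.

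- Fewest envelopes: 80/4 = 20, so 80 − 20 = 60 known (75%).
- Most envelopes: each stratum ends with one patient in its last block, giving (80 − 4)/4 + 4 = 23, so 80 − 23 = 57 known (57/80 = 71%).

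**3. One envelope per patient, block still fixed at 4, assigner still unblinded.** The fourth allocation is always known. The third is known when the first two match.

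| Block distribution | P(first two match) | Expected known per block | Share | Of 80, blocks filled |
|---|---|---|---|---|
| Plan's odd/even rule (AABB and BBAA 1/4 each, other four 1/8 each) | 1/4 + 1/4 = 1/2 | 1 + 1/2 = 1.5 | 1.5/4 = 37.5% | 30 |
| Six equally likely blocks, for comparison | 2/6 = 1/3 | 1 + 1/3 = 1.33 | 1.33/4 = 33.3% | about 27 |

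Splitting the envelopes therefore halves the foreknowledge (75% to 37.5%) but does not restore concealment. The plan's own rule is slightly more predictable than equally likely blocks.

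**The case against.** The strongest reply is that foreknowledge is not steering. Eligibility is confirmed, consent taken, two weeks of run-in completed and baseline blood, urine and ambulatory pressure obtained before anything is dispensed. At the eligibility check, a patient's place in the block still depends on who else in that stratum finishes run-in first. This stands in part. It narrows the opportunity, mainly to retention and to timing of the dispensing visit. It does not close it, since the Run-in section gives testing motivation as one of its purposes and Setting does not separate the eligibility check from the assigner.

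A second reply is that the article condenses a longer protocol. It does not say who opens the envelopes or whether allocations inside are covered singly. This also stands as a limit: that the unblinded investigator sees the whole block is inferred from that person's role. Even so, the sentence states what goes into each envelope, so the point is not a complaint about omitted detail.

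Three stronger readings are tempting but unsupported.

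- A reader might infer that the next three patients in the trial are known. Only the next three in the same block and stratum are.
- A reader might infer a definite bias in mmHg. That would be the between-arm difference in the share of some favourable type of patient, multiplied by that type's extra fall in pressure. The document gives neither quantity.
- A reader might infer that unblinded handling also distorts the biweekly calls and drop-out decisions. The Compliance and Eligibility sections do not say who makes the calls or decides on drop-out, and that would be a different problem from concealment.

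**Conclusion.** The concern holds on the plain reading. The described procedure defeats allocation concealment for up to three in four patients: at most 60 of 80, and 57 to 60 with four non-overlapping strata. Nothing elsewhere in the article repairs it. The result assumes that the envelope shows its full sequence when opened and that the assigning investigator sees it. It demonstrates loss of concealment; it does not show that enrolment was steered, and the effect on the estimated blood-pressure difference cannot be sized from the document. The weakness touches the primary comparison, cannot be reliably repaired in the analysis and is cheap to correct, so it should be corrected before further patients are allocated.

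**What to change.** For all remaining patients, adopt one of these:

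- one sequentially numbered, sealed opaque envelope per participant within each stratum; or
- identical packs numbered separately within each stratum. If the assigner does not know the key, past allocations stay hidden too and nothing can be deduced from them.

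In either case, someone without patient contact should prepare the material, and each allocation should be released only after eligibility and baseline are complete. Vary the block size (for example 4 and 6) and do not disclose it. Start new sequences instead of splitting block envelopes already opened. Report how many patients were allocated from block envelopes.

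Two cautions apply. Data management and monitoring describes a single series of codes from 1 to 80; tying arms to that series would break the stratified allocation, so numbering must run within stratum. The four listed strata also overlap, because every patient has both a diabetes status and a statin status, so state which non-overlapping strata are used before re-packing.

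If single-patient covers already exist inside the envelopes, the text should say so; the fixed block size would still need changing.

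The cost is one re-packing and a recorded, justified amendment, as Protocol amendments requires. Possible imbalance rises slightly: an unfinished block of 6 can leave a difference of 3 in a stratum, against 2 for a block of 4, and abandoning a part-used block adds at most 2 per stratum. Trial status gives recruitment from 2020-01-20 for about five months and a protocol dated 26 March 2020, so the change can reach only patients allocated after it is made.

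### The four randomisation strata are written as the separate levels of two factors, so each participant falls in two strata and no rule says which block list supplies the allocation

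*Protocol article*

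**What the plan says.** The Randomization/blinding section of the protocol article introduces the two factors by observing that "Diabetes and hyperlipidemia are two other major CVD risk factors that may coexist with hypertension". It then gives the purpose: "To achieve a balanced distribution of these risk factors in each of the study groups, stratified block randomization will be performed". The strata are listed as follows: "with four strata: with a history of diabetes, without a history of diabetes, receiving statins, and not receiving statins". The next sentence makes each one operational: "A block size of 4 within each stratum will be used, with a 1:1 randomization between the two groups".

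The same section says that each block's sequence goes into a sealed opaque envelope and that the investigator who assigns patients is not blinded. The Participant recruitment section admits patients with "diabetes and/or hyperlipidemia and/or smoking" in addition to hypertension, so the risk factors can occur together in one person. No other section redefines the strata or says which list takes precedence. The Statistical analyses section plans a parametric or nonparametric ANCOVA that adjusts for baseline levels. It does not mention the stratification factors.

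**The concern.** Strata for blocked randomisation must be mutually exclusive and together cover everyone, so that each new participant points to exactly one list. The listed strata do not meet this. A diabetic patient on a statin belongs to the diabetes stratum and to the statin stratum, each with its own blocks of 4, and the next entries on the two lists may name different arms.

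Two things are at stake:

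- **Reproducibility.** An allocation made under the printed rule cannot be reproduced or audited, because the rule does not say which list applied.
- **Balance.** The stated reason for stratifying is to balance both factors. Following one list per person secures that fully for, at most, the factor the list belongs to. Statin use matters here because the lipid profile is among the secondary outcomes.

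**Working it through.** **1. The plan's own figure.** The Sample size section rests on a trial that "observed a reduction in SBP of 6.2 mmHg compared to placebo", reaching its total "by considering pooled value of the standard deviation = 8.8" and with α "≤ 0.05 and statistical power of 80%, the minimum sample size will be 66 patients". The standardised difference is 6.2/8.8 = 0.705. A two-sided two-sample t test at 0.05 with 80% power needs 32.6, so 33 per arm, which is 66 in total. The stated figure is reproduced, and the point below does not depend on it. The imbalance calculations use the planned recruitment of 80, 40 per arm, from the same section.

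**2. Count of stratum memberships.** This needs no assumption.

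| Participant | Diabetes | No diabetes | Statin | No statin | Strata |
|---|---|---|---|---|---|
| Diabetes, statin | yes | | yes | | 2 |
| Diabetes, no statin | yes | | | yes | 2 |
| No diabetes, statin | | yes | yes | | 2 |
| No diabetes, no statin | | yes | | yes | 2 |

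Every profile falls in exactly two listed strata. If the four lists are independent and each is 1:1, the two entries that apply to a participant disagree with probability 2 × 0.5 × 0.5 = 0.5. A simulation at assumed prevalences of 40% diabetes and 60% statins gave 0.498.

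**3. If only one factor's lists were used.** The other factor is then left approximately to chance. Let X and Y be the numbers with that factor in the two arms, each Binomial(40, p). More than 10 percentage points means |X − Y|/40 > 0.10, so |X − Y| ≥ 5. The document gives no prevalence, so p is assumed:

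- p = 0.5: P(|X − Y| ≥ 5) = 0.314
- p = 0.3 or 0.7: P(|X − Y| ≥ 5) = 0.272
- exactly 40 of the 80 have the factor (hypergeometric): 0.263

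**4. Other rules that staff might have improvised.** Simulation used N = 80, permuted blocks of 4, assumed prevalences of 30% or 50% for diabetes and 50% or 70% for statins, independent of each other. Entries are the arm difference in participants within a factor level.

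| Rule | Diabetes levels, mean (95th percentile) | Statin levels, mean (95th percentile) |
|---|---|---|
| Diabetes lists only | about 0.7 (2) | 3.3–3.6 (8–9) |
| Either applicable list, at random | 2.4–2.7 (6–7) | 2.4–2.6 (6) |
| Diabetes list for diabetics, statin lists for the rest | 0.7–1.0 (2) | 1.9–2.6 (5–6) |
| Crossed cells | about 1.0 (2) | about 1.0 (2–3) |

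**5. Bound under crossed cells.** A block of 4 holds two of each arm, so an incomplete block leaves a cell at most 2 apart. Each factor level is made of two cells, so it can differ by at most 2 + 2 = 4 participants. The largest difference in the simulations was 4.

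**The case against.** The strongest reply is that this is a fault of wording. Two binary factors crossed give exactly four cells, and the article says there are four strata, so the authors may have listed factor levels where they meant cells. The article is condensed and the working lists are not shown. This stands as a limit: an undefined rule in the text is proven, and overlapping lists in use are not. It does not remove the point, because the article states the strata explicitly, and as stated they overlap.

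A reader might infer that the scheme could not have been run at all. The documents do not support that. The sequence preparation is described in the past tense, and the Trial status section says that recruitment started on 20 January 2020, before the protocol version dated 26 March 2020. Some working rule presumably existed, but it is not reported.

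A reader might also infer that the unblinded investigator could freely choose the list that gives the preferred arm. Sealed envelopes hide the entries of unopened blocks, so any such choice would be limited to blocks already opened. Exposure of the rest of an opened block is a separate concealment matter that crossed strata would not cure. Nothing suggests that steering took place.

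Finally, chance imbalance under random allocation does not by itself bias a comparison. Lipids are secondary, patients are told to keep their medication constant, and baseline-adjusted ANCOVA is planned. All of this stands and limits the consequence. It does not supply the missing allocation rule, and adjusting for an outcome's baseline level is not the same as adjusting for diabetes history and statin use. A separate analysis plan may name further covariates. The article states its adjustment, and these two are not in it.

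**Conclusion.** The point holds for the text as written. The listed strata overlap for every participant, no rule selects a list, and the stated aim of balancing diabetes and statin use is therefore not secured. This part rests on no assumption.

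The size of the consequence does rest on assumptions. If one factor's lists served everyone, the chance of an imbalance above 10 percentage points on the other factor is about 31% at an assumed 50% prevalence with 40 per arm, and about 27% at 30% or 70%. An uncorrected normal approximation gives 0.37 at 50% (standard deviation √(0.5 × 0.5 × 2/40) = 0.112), but it overstates the risk for a discrete count. Balance need not fail entirely, since other improvised rules give partial balance on both factors.

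A reader might go further and conclude that the trial's primary result is compromised. The documents do not show this: the sample size of 66 is unaffected, and no bias in the systolic blood pressure comparison is demonstrated.

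**What to change.** Define the strata as the four crossed cells: diabetes with statin, diabetes without statin, statin without diabetes, and neither. Keep one list in blocks of 4 per cell.

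- **If the lists in use are already crossed,** correct the sentence and leave the lists alone. Regenerating them would disturb a sound scheme for no gain.
- **If they are not,** use crossed lists for the remaining participants, and report which list allocated each participant already randomised, while this can still be reconstructed.
- **In either case,** include diabetes history and statin use as covariates in the between-group ANCOVA, alongside the baseline level.

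The cost is one amended sentence in the randomisation section, one in the analysis section and, only if needed, new lists for the remaining participants. The number of lists stays at four and the sample size does not change. With four lists, the overall arm totals can differ by up to 4 × 2 = 8 participants if every cell ends mid-block in the same direction. The simulated mean was about 1.3.
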